#### Aim 1 (primary aim)

Hypothesis 1: Participants living in developments in any of the three intervention groups will increase minutes of moderate intensity physical activity more than participants in control group developments at 24 month follow up.

##### Within group analysis

Preliminary analysis will examine within group differences in each of the study groups from baseline to the end of the intervention at 2 years. Minutes of moderate or greater intensity activity per week will be examined using paired t-test if the distribution is approximately normal or the nonparametric Wilcoxon signed-rank test if normality cannot be assumed. McNemar’s chi-squared test will be used for a paired analysis of meeting recommended physical activity level (binary outcome) pre and post intervention.

##### Between group analysis

The between group hypothesis is tested in three separate bivariate analyses comparing each intervention group to the control group in two primary outcomes based on the cluster-randomized design. We examine change in each primary outcome pre-intervention to post-intervention: 1) the number of minutes of moderate or greater intensity physical activity per week (continuous); and 2) meeting the recommended guidelines of >150 minutes of moderate or greater intensity physical activity per week (dichotomous at individual level, proportion at group level). In addition, we will examine this hypothesis controlling for potential confounding factors and any variables that violate the randomization assumption using multilevel multivariable linear (continuous outcomes) and logistic (binary outcomes) regression models.

Hypothesis 2: Participants living in developments receiving the combined intervention (E+I) will demonstrate even greater increases in the number of minutes of moderate intensity physical activity per week (individual level) and the proportion meeting the recommended physical activity guidelines (development level) from baseline to 24-month follow-up, compared to either intervention delivered singly.

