##### Statistical analysis

This hypothesis is tested in two separate bivariate analysis - one comparing the multilevel intervention group (E+I) to the environment intervention only group (E) and the other comparing the multilevel intervention group (E+I) to the individual level intervention only group (I).

Hypothesis 3: Participants living in developments receiving the combined intervention (E+I) will demonstrate even greater increases in the number of minutes of moderate intensity physical activity per week (individual level) and the proportion meeting the recommended physical activity guidelines (development level) from baseline to 24-month follow-up, compared to the sum of average change in environmental intervention compared to control and the individual level intervention compared to control (synergistic effect).

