##### Statistical analysis

To examine this hypothesis, we exploit our study design which has a multifactorial design embedded in a cluster randomized controlled trial. Multifactorial experimental designs combine the rigor of experimental design with the ability to produce results on the effectiveness of alternate approaches to multicomponent interventions in a single experiment. We will use multilevel regression analysis and test for an interaction effect between the environmental and individual level interventions (E+I). The presence of a significant interaction between E and I on the primary outcome of physical activity suggests synergy between these components of the intervention. If the effects of the environmental level intervention and individual level intervention are additive there should not be a significant interaction in the model. In this case, we can compare the interaction results to the multilevel intervention group (E+I) to examine the exploratory hypothesis that E+I is more effective than E&I combined.

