##### Statistical analysis

Mediation and moderation are examined using variables at both levels, as such we will use multilevel structural equation models and path analysis to examine multilevel mediation and multilevel moderation within and across levels [70, 71]. The multilevel structural equation model framework is flexible and allows for testing models with predictors, mediators, and outcomes on either of the two levels. Given the small number of clusters both the Random Coefficient Prediction (RCP) method and the Latent Moderated Structural Equation (LMS) method with residual bootstrapping to estimate confidence intervals will be used to examine potential moderation. In RCP a random slope is predicted by a moderator. LMS can be applied to multilevel data by creating latent interactions among random coefficients.

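### Hypotheses 1 and 2 are tested in separate two-arm comparisons on 4 df; one four-arm model gives the same contrasts on 8 df, and the Hypothesis 3 reading rule needs a sign and a confidence interval

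*Protocol article*

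**What the plan says.** All references are to the protocol article.

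- **Hypothesis 1** (Between group analysis): "The between group hypothesis is tested in three separate bivariate analyses comparing each intervention group to the control group". The section says these tests are based on the cluster-randomised design. It then adds adjusted models: "In addition, we will examine this hypothesis controlling for potential confounding factors and any variables that violate the randomization assumption using multilevel multivariable linear" and logistic regression. It does not say whether each adjusted model is fitted to two arms or to all four.
- **Hypothesis 2** (Statistical analysis): "This hypothesis is tested in two separate bivariate analysis", namely E+I against E and E+I against I.
- **Hypothesis 3** is stated directionally: the combined arm should exceed the sum of the two separate effects. Its Statistical analysis section uses the factorial structure in a multilevel model with an E x I interaction. It says that a significant interaction suggests synergy, without a condition on sign. It then says that additive effects should give no significant interaction, and that in this case the team can "compare the interaction results to the multilevel intervention group (E+I) to examine the exploratory hypothesis that E+I is more effective than E&I combined".
- **Design** (Design of the Community Walks study; Recruiting public housing developments): 12 developments, 8 run by the Boston Housing Authority and 4 private, 3 per arm, randomised with stratification by management company.
- **Power** (Aim 1 - between group analysis sample size): a two-group test with 3 clusters of 32 per group, more than 90% power for 5 minutes, by a mixed model at 0.05.
- **Small-sample measures**: "Given the small number of clusters" appears in the Aim 2 analysis, as the reason for the moderation methods. The Aim 1 analysis text has no counterpart.

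**The concern.** In a cluster trial the precision of an arm comparison is judged against variation between developments. A test restricted to two arms sees six developments and has 6 - 2 = 4 df for that variation. The other six carry information on the same variance, and the factorial model already planned for Hypothesis 3 would use it. With so few clusters, the step from 4 to 8 df matters: the critical value falls noticeably, and so does the effect needed for a given power. The primary aim is therefore tested with the weaker of two structures that the protocol already contains.

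Hypothesis 3 has a related problem of interpretation. The hypothesis has a direction but the written reading rule has none. A non-significant interaction leads into the additive case and a further comparison, although the interaction is the least precise contrast in the trial.

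**Working it through.** **1. The plan's own figure.** The variance of a difference between two arms is 2 x SD² x [1 + (m - 1) x ICC] / (k x m). With k = 3 and m = 32 this is 2 x SD² x (1 + 31 x ICC) / 96. The stated power of more than 90% for 5 minutes cannot be reproduced without SD and ICC. The SD at which power is exactly 90% (two-sided 0.05, assumed) is:

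| ICC (assumed) | Normal | 4 df | 8 df |
|---|---|---|---|
| 0 | 10.7 | 7.9 | 9.3 |
| 0.01 | 9.3 | 6.9 | 8.2 |
| 0.05 | 6.7 | 4.9 | 5.8 |
| 0.10 | 5.3 | 3.9 | 4.6 |

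**2. Degrees of freedom.** Df = developments minus fitted cluster-level parameters. Two arms: 6 - 2 = 4, or 3 with the stratum. Four arms: 12 - 4 = 8, or 7 with the stratum.

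**3. Same contrasts, same true SE.** Let v be the variance of a development mean. Each arm mean has variance v/3, so every Hypothesis 1 or 2 contrast has variance 2v/3, both in a two-arm test and in the model with E, I and E x I. The gain is only in how well v is estimated. Halving the contrast variance to v/3 (on 9 df) would need a model without E x I, which conflicts with testing Hypothesis 3.

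**4. Size of the gain.** An effect with 90% power under normal theory lies 1.960 + 1.282 = 3.24 SE from zero. Noncentral t power at that distance:

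| Analysis | df | Critical t | Power | Effect for 90% power |
|---|---|---|---|---|
| Two-arm | 4 | 2.776 | 68% | 4.40 SE |
| Four-arm | 8 | 2.306 | 81% | 3.71 SE |
| Two-arm + stratum | 3 | 3.182 | 59% | 5.01 SE |
| Four-arm + stratum | 7 | 2.365 | 79% | 3.80 SE |

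Without the stratum, the critical value falls by 1 - 2.306/2.776 = 17% and the detectable effect by 1 - 3.71/4.40 = 16%. The stratum rows take the stratum as balanced across arms (2 Boston Housing Authority and 1 private each). This is inferred from 8 + 4 developments and the stratification. A simulation of development means (200,000 runs) gave power of 68.3% and 81.0%, and type I error of 4.9% for both t tests.

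**5. Price of pooling.** Suppose, as an assumption, that between-development variance is twice as large in E and E+I as in I and control. Simulated type I error (400,000 runs) of the pooled 8-df test is then about 8% for E+I against E, 2.4% for I against control, and about 5% for E or E+I against control. The pairwise 4-df tests stay at about 5%.

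**6. Interaction.** E x I has variance 4v/3, so its SE is √2 times the pairwise SE. Take a pairwise effect with 90% power on 8 df (3.71 SE). An interaction of equal size lies 3.71/1.414 = 2.63 of its own SEs from zero and has about 63% power. It would be missed more than one time in three.

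**The case against.** Pairwise testing is a legitimate choice. On 4 df it holds its type I error, gives the same point estimates, and does not borrow a variance from arms outside the comparison. Three developments per arm cannot verify a common variance, and step 5 shows what a wrong assumption would cost. This stands, and it is why the pairwise tests should be kept as a sensitivity analysis.

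The 68% and 81% rest on a benchmark of exactly 90% normal-theory power, whereas the protocol claims more. If the paired t-test line under Aim 1 - within group analysis sample size (n = 21, difference 3.0, 90% power) is read as an SD of change of about 4.03, power for 5 minutes at an ICC of 0.05 is already 97% on 4 df. At 0.10 it is 88% on 4 df against 96% on 8 df. That reading is itself an assumption, but it shows that the practical loss may be small.

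The adjusted multilevel models might already pool all four arms. The text does not say so, they come in addition to the separate tests, and the power statement is two-group.

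Stronger readings are tempting but not supported:

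- A reader might infer inflated type I error. A normal reference would give about 12% on 4 df, but the article names no reference distribution, and the df method is a detail that such an article may leave to the analysis plan.
- A reader might say that half the clusters are discarded. They are left out of each comparison, not out of the trial.
- A reader might say that the plan will report antagonism as synergy. Hypothesis 3 itself is directional; only the reading rule omits the sign. The follow-up comparison is labelled exploratory and its wording is unclear, so calling it the same null retested is only one reading.

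**Conclusion.** The point holds as one of efficiency and clarity, not of validity. The stated tests of Hypotheses 1 and 2 use 4 df where the trial's own factorial structure offers 8 (3 against 7 with the stratum). At the 90% normal-theory benchmark this costs 13 percentage points of power (81% - 68%), or 20 with the stratum (79% - 59%). The figures assume cluster-level df, a two-sided test at 0.05, a continuous outcome and a common between-development variance. They are relative, because absolute power cannot be established without SD and ICC.

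For Hypothesis 3 the smaller point stands: the rule should carry the sign that the hypothesis already has, and at about 63% power for an interaction as large as a well-powered pairwise effect, non-significance is not evidence of additivity.

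**What to change.** - Make the primary analysis one linear mixed model on all 12 developments with E, I, E x I, the management stratum and a random development effect, using a small-sample df method such as Kenward-Roger or Satterthwaite.
- Prespecify the three Hypothesis 1 comparisons, the two Hypothesis 2 comparisons and the Hypothesis 3 interaction as contrasts from that model.
- Keep the pairwise t tests as a sensitivity analysis for unequal between-development variance.
- For Hypothesis 3, report the E x I contrast in minutes with its 95% CI. State that synergy is supported only if the contrast is positive and the whole interval lies above zero. Call a non-significant interaction inconclusive, and delete the follow-up comparison of E+I with the two components combined.

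The cost is wording only, with no new data and no change to the design. The downside is the common-variance assumption. The change should be fixed before outcomes are examined by arm.

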**Methods:**

The study design is a prospective, cluster randomized controlled trial, with housing developments (*n=*12) as the units of randomization. In a four-group, factorial trial, we will compare an environmental intervention (E) alone (3 developments), an individual intervention (I) alone (3 developments), an environmental plus individual (E+I) intervention (3 developments), against an assessment only control group (3 developments). The environmental only intervention consists of community health workers leading walking groups and indoor activities, a walking advocacy program for residents, and provision of walking maps/signage. The individual only intervention consists of a 12-week automated telephone program to increase physical activity motivation and self-efficacy. All residents are invited to participate in the intervention activities being delivered at their development. The primary outcome is change in moderate intensity physical activity measured via an accelerometer-based device among an evaluation cohort (*n=*50 individuals at each of the 12 developments) from baseline to 24-month follow up. Mediation (e.g., neighborhood walkability, motivation) and moderation (e.g., neighborhood stress) of our interventions will be assessed. Lastly, we will interview key informants to assess factors from the Consolidated Framework for Implementation Research domains to inform future implementation.

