#### Primary outcome measurement: physical activity

Our primary outcome is minutes of moderate intensity daily physical activity. Participants will wear an ActiGraph GT3X+ accelerometer-based device on their hip and the device will be initialized to collect raw data at 30 Hz. The participant will be instructed to wear the device during waking hours every day for 7 days, except during water activities. At minimum, the GT3X+ must be worn for 10 waking hours/d on at least 4 days. Initially, the raw GT3X+ data will be used to estimate time spent in MVPA (physical activity at ≥ 3.0 metabolic equivalents units) using publicly available algorithms developed for adults [68]. The use of this algorithm will also allow for the detection of continuous walking and running bouts to help confirm participants engagement. All device data will be cleaned and processed [69] in R. As updated algorithms and machine learning models are developed, we will explore use of updated techniques to maximize the data outcomes.

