#### Aim 1 - between group analysis sample size

We power the multivariable analysis based on test for two means in a 2-level hierarchal design with level 2 randomization. Sample sizes of 96 subjects in each group, which were obtained by sampling 3 clusters with an average of 32 subjects per cluster, achieve >90% power to detect a difference between the group means of at least 5 minutes (or 5 percent difference in meeting recommended levels). A test based on a mixed-model analysis at a significance level of 0.05.

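### The between-group analysis names two primary outcomes where the rest of the protocol names one, so the result that decides the primary aim is not fixed

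*Protocol article*

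**What the plan says.** Four places in the protocol article treat the primary outcome as single:

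- Abstract, Methods: "The primary outcome is change in moderate intensity physical activity measured via an accelerometer-based device".
- Primary outcome measurement: "Our primary outcome is minutes of moderate intensity daily physical activity".
- Aim 1, Hypothesis 1, is framed in minutes only. It predicts that participants in "developments in any of the three intervention groups will increase minutes of moderate intensity physical activity" more than those in control developments.
- The statistical analysis for Hypothesis 3 looks for an interaction that, "on the primary outcome of physical activity suggests synergy", again in the singular.

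The Between group analysis section, which tests Hypothesis 1, specifies three separate comparisons, "comparing each intervention group to the control group in two primary outcomes based on the cluster-randomized design". It numbers the two outcomes: "the number of minutes of moderate or greater intensity physical activity per week (continuous"), and "meeting the recommended guidelines of >150 minutes of moderate or greater intensity physical activity per week".

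That section gives no significance level. The only level attached to the between-group comparison is in the sample-size section: "A test based on a mixed-model analysis at a significance level of 0.05". The power sentence before it covers a difference of 5 minutes or, in brackets, 5 percent in meeting recommended levels.

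**The concern.** A reader cannot tell from the protocol whether a trial that is positive on guideline status and negative on minutes, or the reverse, has met its primary aim. Either result could be presented as primary with support from the text. Two further points widen the choice. There are three comparisons against one shared control, so two outcomes make six tests. Hypothesis 1 also speaks of *any* of the three intervention groups without saying whether that means each of them or at least one. At stake is the chance of a false positive primary claim, and the standing of the primary result once the data are known.

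**Working it through.** **Step 1. Count the primary outcomes by section.**

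| Section | Primary outcomes | Content |
|---|---|---|
| Abstract, Methods | 1 | change in moderate-intensity activity, by device |
| Primary outcome measurement | 1 | minutes, daily |
| Aim 1, Hypothesis 1 | 1 | minutes |
| Hypothesis 3 analysis | 1 | physical activity, singular |
| Between group analysis | 2 | weekly minutes; meeting the guideline |

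Hypotheses 2 and 3 also use the proportion meeting the guideline, but do not call it primary. The conflict is in the text itself and does not depend on any document not shown. The time unit also differs, daily in one section and weekly in another.

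**Step 2. Count the tests.** 3 arms against control × 2 outcomes = 6.

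**Step 3. The plan's own figure.** The protocol states no family-wise error rate, so there is none to reproduce. Its stated power (>90% with 96 per arm, 3 developments × 32) cannot be reproduced either, because no standard deviation or intracluster correlation is given.

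**Step 4. False rejections with no true effect.** Assumptions, none of them stated in the protocol as a decision rule: each test two-sided at 0.05; any one significant test counts as success; no other multiplicity rule; correlation rho between the two outcomes.

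Bounds for independent tests: 1 − 0.95³ = 14.3% for three tests, and 1 − 0.95⁶ = 26.5% for six.

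The shared control makes the comparisons correlated (0.5 with equal arms). Simulation with four equal arms and normal tests gives:

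| Tests | rho | At least one rejection, either direction | At least one false claim of benefit |
|---|---|---|---|
| 3 (minutes only) | – | 12.5% | 6.3% |
| 6 | 0 | 23.5% | 12.1% |
| 6 | 0.5 | 22.0% | 11.1% |
| 6 | 0.7 | 20.3% | 10.2% |
| 6 | 0.8 | 19.0% | 9.5% |
| 6 | 0.9 | 17.2% | 8.6% |
| 6 | 1 | 12.5% | 6.3% |

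Cluster-level t-tests with 3 developments per arm and separate variances give similar values: 22.7%, 21.4% and 20.2% at rho 0.5, 0.7 and 0.8. With a variance pooled over the four arms (8 df) they are 21.0%, 19.4% and 18.4%.

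The protocol gives no value for rho. In an illustrative normal model, change in minutes and change in a dichotomised version of it correlate at about 0.58 to 0.74, which is why 0.5–0.8 is used as the working range.

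**Step 5. Other success rules, same simulation.** If all three arms must beat control on minutes, false success is about 0.2%. If both outcomes must show benefit in the same arm, for at least one arm, it is about 1.3% (rho 0.5) to 2.9% (rho 0.8).

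**Step 6. Cost of controlling three comparisons.** With 12 developments in 4 arms there are 12 − 4 = 8 df. The two-sided 5% critical t is 2.31; the Dunnett value for three comparisons is about 2.88. In normal terms, a test with exactly 90% power at 0.05 has signal 1.960 + 1.282 = 3.242. At 0.05/3 = 0.0167 the critical value is 2.394, leaving 3.242 − 2.394 = 0.848, or about 80% power.

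**The case against.** A reader might infer that the protocol runs all six tests at 0.05 and so carries a family-wise error of about 20%. The document does not say that. The 0.05 stands in the sample-size section and shows how power was calculated; the analysis section gives no level. Multiplicity handling is commonly left to a statistical analysis plan, which is not shown here, so its absence from a journal article is not a fault. This part of the objection stands.

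Nor does the protocol say that one significant test of six is enough. The Discussion paragraph of the abstract lists the three arms by name and can be read as a prediction for each. If the comparisons are three separate hypotheses, each carries its own 5% error, and statisticians differ on whether distinct arms need joint adjustment. Under stricter rules the error is far below 20% (Step 5). The two-sided figures also count findings that an intervention is worse than control; false claims of benefit are about half as frequent. All of this stands too, and it limits what the percentages can support.

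What the objection does not remove is the contradiction. Sections of the same document give different answers on how many primary outcomes there are. An analysis plan could choose between them, but the published protocol would still support either choice.

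**Conclusion.** The contradiction holds with high confidence: the Between group analysis section names two primary outcomes, while the abstract, the measurement section and the Hypothesis 3 analysis name one and Hypothesis 1 concerns minutes alone. The meaning of *any* in Hypothesis 1 is also left open.

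The error rate is conditional. If each of six tests were run at 0.05, any one sufficed and no further rule applied, there would be about a 19–22% chance of at least one false rejection (rho 0.5–0.8; full range 12.5% to 23.5%) and about 9.5–11% of a false claim of benefit. Dropping the second outcome from primary status brings these to about 12.5% and 6.3%. So a single primary outcome removes the choice between outcomes, but does not by itself bring the error over three arms to 5%. Whether that remainder needs control depends on what Hypothesis 1 is meant to claim.

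**What to change.** In the Between group analysis section, name minutes of moderate-or-greater intensity activity as the single primary outcome, in line with the abstract, the measurement section and Hypothesis 1, and use one time unit throughout. Make meeting the guideline a secondary outcome. This is a wording change; the small cost is that guideline status can no longer support a primary claim. It should be made before outcome data are examined by arm.

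Also state whether Hypothesis 1 refers to each intervention arm or to at least one. If at least one, control the error over the three comparisons, for example by a fixed sequence or Holm, and restate power at that level. This is more than wording. Power must be recalculated with a stated standard deviation and intracluster correlation, and with three developments per arm the loss is real (Step 6). A fixed sequence costs nothing for its first comparison, but blocks formal claims on the later ones if the first fails.

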### Recruitment – public housing developments and residents

#### Recruiting public housing developments

Developments are eligible for selection as one of our study sites if they have at least 100 units. A statistician conducted the randomization stratified by management company (Boston Housing Authority/Private) using a computer program, such that 3 developments went to the E group, 3 developments went to the I group, 3 developments went to the E+I group, and 3 developments went to the control.

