#### Recruitment and screening of the evaluation cohort

We propose to recruit 50 participants per development in the evaluation cohort. Eligibility criteria include being able to speak English or Spanish, being 18 years old or older, being a public housing resident from one of our study sites, not planning to move within the next 2 years, having access to a phone, not currently participating in another physical activity study, being able to walk independently without regular need for special equipment (wheelchair, scooter, or walker), ability to provide informed consent, and willingness to complete the accelerometer-based device measurement. By design, the entire cohort will be low-income.

Recruitment will take place at the developments, using common sampling rules and a direct household door-knocking approach [39–41]. Trained Research Assistants will approach units based on an assigned list and will attempt to identify an eligible resident using a brief script. The survey steps will be as follows: approach the unit, attempt to identify a resident, describe the study, determine eligibility, collect informed consent documents, collect the survey measurements, explain the physical activity device, and remind the residents of follow-up visits. Data collection documents for screening, documenting informed consent, and baseline, 12- and 24-month assessments are stored in REDCap [42].

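### Aim 1 names multilevel logistic and linear models for 6 to 12 developments with no small-sample provision; under default Wald inference the guideline outcome's type I error would be about 0.06 to 0.16 at ICC 0.01 to 0.05

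*Protocol article*

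**What the plan says.** All places are in the protocol article.

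- **Between group analysis.** Hypothesis 1 is first "tested in three separate bivariate analyses comparing each intervention group to the control group in two primary outcomes based on the cluster-randomized design". As a further step it is examined with confounders controlled, "using multilevel multivariable linear (continuous outcomes) and logistic (binary outcomes) regression models". The two outcomes are minutes of activity per week and meeting the guideline of more than 150 minutes.
- **Statistical analysis under Hypothesis 3.** Synergy has one test: "We will use multilevel regression analysis and test for an interaction effect between the environmental and individual level interventions (E+I").
- **Aim 1 - between group analysis sample size.** The multivariable analysis is powered on "Sample sizes of 96 subjects in each group, which were obtained by sampling 3 clusters with an average of 32 subjects per cluster", with the closing statement "A test based on a mixed-model analysis at a significance level of 0.05".
- **Recruiting public housing developments.** "3 developments went to the E group, 3 developments went to the I group, 3 developments went to the E+I group", and 3 went to control.
- **Recruitment and screening of the evaluation cohort.** "We propose to recruit 50 participants per development in the evaluation cohort".
- **Statistical analysis under Aim 2.** Here the article does react to the design: "Given the small number of clusters both the Random Coefficient Prediction (RCP) method and the Latent Moderated Structural Equation (LMS) method" are used, with residual bootstrapping for the intervals.

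For Aim 1 the article gives no ICC, estimation method, degrees of freedom or reference distribution.

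**The concern.** A random-intercept logistic model is usually fitted by maximum likelihood and tested with a Wald z. That approximation needs many clusters. With 6 or 12, the between-development variance is estimated poorly and often as zero. The model then treats residents of one development as independent, and the standard error is too small. The same 12 developments carry Aim 1 and Aim 2, yet only Aim 2 moderation has a provision for their small number.

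At stake are the adjusted result for guideline attainment, which this section counts among two primary outcomes, and any claim that the combined intervention is more than additive. The adjusted models are likely to matter, because the Analysis plan sends every unbalanced baseline characteristic into them and 12 clusters will rarely balance well.

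**Working it through.** **1. What the article's own figures reveal about the test.** The Aim 1 power of more than 90% cannot be reproduced for minutes, because neither SD nor ICC is given. With SE = SD × √(2 × [1 + 31 × ICC] / 96) and a difference of 5 minutes, 90% power at ICC 0 needs SD of at most 10.7 with a normal reference, or about 7.9 with t on 4 df. Either reading is possible.

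The LMS calculation (492 residents, 41 per development, interaction difference 3.75, power above 85%) does not settle it either. Take SD 4, close to the 4.03 implied by the paired t-test figures, and ICC 0.05. Then SE = √(4 × 16 × [1 + 40 × 0.05] / 123) = 1.249, and 3.75/1.249 − 1.96 = 1.04, so power is 85.1% with a normal reference. A t on 8 df gives 74.8%. But t on 8 df with an ICC near 0.033 also gives 85%, and any pair with SD² × (1 + 40 × ICC) = 48 gives the normal result (SD 5 with ICC 0.023, for example).

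**2. Tail check.** Between-development df are 6 − 2 = 4 for one arm against control, and 12 − 4 = 8 in a four-arm model. If a statistic that follows t is compared with 1.96, P(|t₄| > 1.96) = 0.122 and P(|t₈| > 1.96) = 0.086, against a stated 0.05.

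**3. Logistic model, simulated with no effect.** Inputs:
- 3 developments per arm, with 32 residents each (power calculation) or 50 (recruitment target).
- Base rate 1 − 0.62 = 0.38, from the 62% with insufficient activity in the Participants section.
- Assumed ICC 0 to 0.10, beta-binomial developments of equal size, follow-up outcome only, no covariates.
- Maximum likelihood by 25-point quadrature, 2,000 replicates per setting (Monte Carlo standard error about 0.004 to 0.009).

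Each cell shows Wald z / same model with t on 4 or 8 df / development-level t test.

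| Developments × residents | ICC 0 | ICC 0.01 | ICC 0.02 | ICC 0.05 |
|---|---|---|---|---|
| 6 × 32 | 0.040 / 0.004 / 0.045 | 0.064 / 0.010 / 0.042 | 0.085 / 0.019 / 0.046 | 0.136 / 0.047 / 0.052 |
| 6 × 50 | 0.044 / 0.005 / 0.043 | 0.080 / 0.015 / 0.040 | 0.107 / 0.027 / 0.049 | 0.159 / 0.062 / 0.051 |
| 12 × 32 | 0.047 / 0.022 / 0.050 | 0.070 / 0.038 / 0.050 | 0.096 / 0.054 / 0.051 | 0.132 / 0.075 / 0.043 |
| 12 × 50 | 0.048 / 0.021 / 0.051 | 0.094 / 0.044 / 0.046 | 0.114 / 0.067 / 0.051 | 0.145 / 0.087 / 0.049 |

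At ICC 0.10 the Wald z rates are 0.137 to 0.199. Over all settings the t reference gives 0.004 to 0.088, too strict at low ICC and too lenient at high ICC, while the development-level test gives 0.040 to 0.056. At ICC 0.02 with 32 residents, the development variance was estimated as zero in 52% of fits with 6 developments and 47% with 12. A smaller run of the logistic E × I contrast (500 replicates, 12 × 32, ICC 0.01 to 0.05) gave 0.07 to 0.12 with Wald z.

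**4. Linear model, same layout, 200,000 replicates.** Over ICC 0.02 to 0.05, ML with z gives 0.099 to 0.158 and REML with z gives 0.068 to 0.108. REML with t on between-development df gives 0.015 to 0.048, with no inflation. For the E × I contrast with 12 developments (400,000 replicates), ML with z gives 0.10 to 0.14, REML with z 0.07 to 0.08, and a development-level t on 8 df gives 0.05.

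**The case against.** A reader might infer that Aim 1 rests on large-sample inference and that guideline attainment will be declared significant two to three times too often. The article supports neither.

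- **The reference distribution is not stated.** Degrees-of-freedom methods are commonly left to an analysis plan that is not shown, so silence on them is no defect in itself. This stands, and it is why the rates are conditional. What remains is the choice of model: for the logistic model, adding a t reference still leaves the test off nominal.
- **The ICC is not given.** The multiple runs from 0.064/0.05 = 1.3 to 0.159/0.05 = 3.2 for ICC 0.01 to 0.05, and there is no inflation at ICC 0. The LMS power figure cannot anchor an ICC, least of all for a binary outcome.
- **The named models are the additional analysis.** The bivariate tests come first and are tied to the cluster-randomized design. The guideline outcome is also described there as a proportion at group level, so a development-level comparison may already be intended. Nothing here shows those tests to be affected.
- **Minutes are the primary outcome elsewhere.** The Abstract, Table 1 and the primary outcome section name accelerometer-measured activity. Only Between group analysis also calls guideline attainment primary.
- **The synergy test is not called logistic.** That follows only if Hypothesis 3, which covers both outcomes, is tested on the binary one.
- **The simulation simplifies.** The plan analyses change with covariates, and 38% comes from self-report rather than accelerometry.

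**Conclusion.** The point holds in conditional form. Aim 1 names multilevel logistic and linear models for 6 to 12 developments and makes no provision for that number, although the article makes one for Aim 2 moderation.

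If default Wald z inference is used, the adjusted test of guideline attainment has a type I error of about 0.06 to 0.16 for assumed ICCs of 0.01 to 0.05. This rests on a 38% base rate, equal developments and no covariates. A joint model with all 12 developments does not remove the problem. The linear model is at risk only with a normal reference.

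To read this as a demonstrated error in the primary result would go too far. It is a worthwhile and cheap improvement to the adjusted and synergy analyses, not a must-fix error.

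**What to change.** **Guideline outcome.** Make the adjusted test, and any E × I test on this outcome, a two-stage analysis. First regress guideline attainment on the resident-level covariates, leaving arm out, and form one adjusted summary per development (observed minus expected proportion, for example). Then analyse the 12 summaries in the four-arm model with terms for E, I and E × I, using a t reference on 12 − 4 = 8 df, or 7 with the management stratum. This pools between-development variance across arms, which should be stated as an assumption. With proportions as summaries, the interaction is on the additive scale, which matches Hypothesis 3's comparison with a sum of average changes.

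**Minutes.** Keep the multilevel linear model, fitted by REML with Kenward-Roger or between-cluster degrees of freedom. State that the development effect stays in the model when its variance is estimated as zero. Use the same rule for the E × I test.

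**Cost.** The change is to analysis wording only, with no new data. Intervals become about 18% wider (2.306/1.960 = 1.18 for t on 8 df against z), and slightly more on 7 df. The guideline effect would be reported as a difference in proportions if that summary is chosen, rather than as an odds ratio. The change should be made before outcomes are analysed.
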